### Treatments

MCT will be based on the published treatment manual developed by Wells [21, 22] consisting of up to 12 sessions of individual treatment. Clients allocated to the EMDR condition will complete 12 sessions based on the structured protocol developed by Shapiro [11]. Sessions for both treatments will be held on a weekly basis and will initially last 45–60 minutes. Participants will be asked to complete further assessments to monitor their progress at the mid-point of therapy, end of treatment and 12 month follow-up. We chose EMDR as a comparator for two primary reasons: First, EMDR is usually regarded as an evidence-based treatment for PTSD to which MCT has not previously been compared. Second, at the clinic where the trial is conducted, EMDR is already an established and widely used treatment. The session content for both conditions is prescribed in detail and manualised.

MCT consists of session 1: case conceptualisation and socialisation; session 2–3: detached mindfulness and worry/rumination postponement and commencement of challenging negative beliefs about symptoms and positive beliefs about worry and rumination; session 4–5: generalising techniques and banning gap-filling and other coping strategies with work on residual beliefs; session 6–7: attentional modification; session 8–9: utilising techniques and work on residual maladaptive coping strategies and beliefs; and session 10–12: developing and consolidating a therapy blueprint and new plan for guiding cognition and action in response to intrusions and symptoms.

The sessions in EMDR are session 1: history and forming an alliance; session 2–3: preparation and target for exposure, including psychoeducation and creating a safe place; session 4–10: desensitisation and reprocessing, which in essence consists of imaginal exposure to the trauma memory and cognitive restructuring of trauma-related cognitions and floatback; and session 11–12: plan relapse prevention, arrange follow up.

### Treatment adherence and fidelity

The therapists delivering the therapies are clinical psychologists who are trained in trauma-focused therapy and have at least 2 years experience. The therapists delivering MCT will be trained in MCT by the originator of the treatment (AW). They will also receive weekly supervision from [name]. The therapists delivering EMDR are all certified level-2 EMDR practitioners who have completed at least EMDR level-2 training and will be supervised by [name], who is an EMDR Europe Approved Senior Trainer. Adherence to the treatments and treatment fidelity will be monitored and assessed using session by session treatment checklists completed by the therapists and monitored in supervision. Rating of checklists will assess the presence of specific therapy components and the absence of prohibited components in both treatments. All treatment sessions will be videotaped and a random sample of 10% of the tapes stratified by session and groups will be rated by experts in the treatments to determine adherence and competency.

### Concomitant care

Participants enrolled in the trial are allowed to continue psychopharmacological treatment as long as they maintain a stable dose throughout the trial. No other concomitant care will be allowed during the trial.

### Data analysis plan

All data will be analysed based on an intention-to-treat (ITT) approach with all randomized patients entering the analysis. Missing data will be estimated by SPSS multiple imputation on the primary measure to estimate the scores of those with missing data. The number of imputations will depend on the amount of missing data. The primary outcome is a continuous longitudinal measure (PDS), therefore linear mixed-model analysis (LMM) will be run. Random effects will be applied to the patient-specific intercepts and covariates will be included in all analyses based on imbalance between trial arms. The effects of the treatments will be examined using the interaction effect of group × time from the mixed-effects analysis with PDS post-treatment as the primary outcome.

In addition to the primary analyses we will conduct exploratory moderation and mediation analyses. Moderation analyses will be conducted with both individual and combined moderators [48, 49]. Mediation analyses [50, 51] will be conducted with PDS as the outcome and PTCI, MCQ-30 and SRS as potential mediators.

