## Methods

### Study design

The study is a two-arm randomized controlled superiority trial with a pre-post and 12-month follow up comparing the effectiveness of MCT and EMDR in the treatment of PTSD. The primary hypothesis is that MCT will be superior to EMDR in reducing PTSD symptoms measured with the PDS post-treatment. The secondary hypothesis is that superiority of MCT will be maintained at 12-month follow up. Stratified randomization where equal numbers of participants are allocated to each condition according to chronicity of PTSD, presence and severity of borderline personality traits (four criteria fulfilled) and gender will be used. The independent variable is a manualised MCT condition (12 sessions) or manualised EMDR (12 sessions). The other secondary outcome measures are the Impact of Events Scale-revised (IES-R), posttraumatic symptoms assessed using the Posttraumatic Stress Scale-Interview (PSS-I), depression assessed using the Beck Depressions Inventory (BDI)-II, anxiety levels assessed using the Beck Anxiety Inventory (BAI)-II, and metacognitions assessed using the Metacognitive Questionnaire (MCQ)-30). The present protocol has been prepared in accordance with relevant items from the SPIRIT Checklist (see Additional file 1) and the SPIRIT Figure (Fig. 1).

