#### Sample size estimation

We assume similar post-treatment scores on the PDS as reported by Wells and colleagues [26] in their comparison of MCT with prolonged exposure, where M = 10.4 for MCT and M = 18.3 for the PE condition, with a pooled standard deviation of 10.6. It is estimated that for a two-tailed superiority trial, 58 patients are required in total (29 per arm) to have an 80% chance of detecting a significant difference in the primary outcome measure at the 5% level. We will aim to recruit more patients than this in order to compensate for dropouts.

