### Randomization

Participants meeting the inclusion criteria are randomized to either EMDR or MCT. Randomization is stratified on gender and borderline personality disorder characteristics, as both gender and BPD characteristics have been found/are assumed to impact treatment outcome. Before initiating the trial the principal investigator ([name]) generated a random-number table using SPSS. Due to the use of a printed random-number table the allocation is not absolutely/perfectly concealed. Authors [name] and [name] assign allegeable participants to the conditions based on the pre-defined random-number table.

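### Covariates for every analysis, including the primary one, are to be picked from observed arm imbalance; the stratification factors and baseline PDS should be fixed in advance, with their form of entry stated

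*Protocol article*

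**What the plan says.** The Data analysis plan fits a linear mixed model to PDS. On random effects it says "Random effects will be applied to the patient-specific intercepts". In the same sentence it adds that "covariates will be included in all analyses based on imbalance between trial arms". The treatment effect is then examined "using the interaction effect of group × time from the mixed-effects analysis with PDS post-treatment as the primary outcome". No section names a covariate, sets a threshold for imbalance, or says whether a covariate enters as a main effect or with time.

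Two sections describe the strata. Under Randomization: "Randomization is stratified on gender and borderline personality disorder characteristics", the reason being that "both gender and BPD characteristics have been found/are assumed to impact treatment outcome". Under Study design, stratified randomization "according to chronicity of PTSD, presence and severity of borderline personality traits (four criteria fulfilled) and gender will be used". Chronicity appears in the second list and not in the first.

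**The concern.** A covariate earns its place in a trial model by predicting outcome, not by happening to differ between arms. A rule triggered by imbalance gets this backwards for stratification factors. The design pushes them towards balance, so the rule tends to drop the variables that the sponsor thought important enough to stratify on. If such a factor carries variance in the tested contrast, that variance stays in the error term, although the design has already removed it from the arm difference. The standard error is then too large.

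The second problem is that the primary model cannot be written down until arms have been compared, and the criterion for that comparison is not stated. At stake are the calibration and power of the primary test, and a reader's ability to confirm that the reported model was the planned one.

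**Working it through.** **1. The plan's own figure.** Inputs from Sample size estimation: "where M = 10.4 for MCT and M = 18.3 for the PE condition, with a pooled standard deviation of 10.6", two-sided 5%, 80% power. The difference is 18.3 − 10.4 = 7.9.

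n per arm = 2 × [10.6 × (1.960 + 0.842) / 7.9]² = 28.26, rounded up to 29, so 58 in total. The stated size reproduces. It is an unadjusted post-score calculation, so it does not depend on the covariate rule.

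**2. An omitted, balanced stratum.** Let V_res be the within-stratum variance of the tested contrast and V_str the variance that the stratum adds to it. The true squared standard error is 2V_res/n, but the model without the stratum estimates about 2(V_res + V_str)/n. Hence

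type I error ≈ 2Φ(−1.96 × √[(V_res + V_str)/V_res]).

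**3. Applied to group × time.** With complete scores at baseline and post-treatment, this interaction is the arm difference in mean change. Assumptions, none of them in the documents: post-treatment variance scaled to 1; the stratum explains a share R of it; its baseline shift is k times its post shift; residual variance is 1 − R at both times with correlation 0.5; the stratum is exactly balanced. Then V_res = 2(1 − R)(1 − 0.5) = 1 − R, and V_str = R(1 − k)².

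For power, take 100 randomised with 25% attrition (the upper figure cited in the Discussion), about 38 per arm. Take a true difference that gives 80% power unadjusted: (1.960 + 0.842) × √(2/38) = 0.643 SD, so 0.643 × √19 = 2.80. Power without the stratum ≈ Φ([2.80 − 1.96√(V_res + V_str)]/√V_res). Power with stratum × time ≈ Φ(2.80/√V_res − 1.96).

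| R | k | V_res | V_str | Type I, omitted | Power, omitted | Power, stratum × time |
|---|---|---|---|---|---|---|
| 0.16 | 1 | 0.84 | 0 | 5.0% | 86.4% | 86.4% |
| 0.16 | 0.5 | 0.84 | 0.04 | 4.5% | 85.3% | 86.4% |
| 0.16 | 0 | 0.84 | 0.16 | 3.2% | 82.1% | 86.4% |
| 0.25 | 1 | 0.75 | 0 | 5.0% | 89.9% | 89.9% |
| 0.25 | 0.5 | 0.75 | 0.0625 | 4.1% | 88.4% | 89.9% |
| 0.25 | 0 | 0.75 | 0.25 | 2.4% | 83.4% | 89.9% |

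Simulation at 38 per arm agrees within its error: type I error was 4.8–5.2% for k = 1, 4.1–4.7% for k = 0.5, and 2.5–3.4% for k = 0.

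**4. Baseline-adjusted post-treatment contrast with strata.** The residual variance is (1 − R)(1 − 0.5²), which is 0.63 or 0.5625. Power ≈ Φ(2.80/√0.63 − 1.96) = 94% or Φ(2.80/√0.5625 − 1.96) = 96%; simulation gives about 93–96%. The change contrast without strata has 82–90%. Much of this gain comes from conditioning on baseline PDS; the strata alone account for 0 to 6.5 points in the table.

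**5. Form of entry.** In test fits of a random-intercept model to complete simulated data, adding a time-invariant covariate as a main effect left the group × time result unchanged: estimate −2.05, SE 1.929 both times. Adding covariate × time moved it to −2.751, SE 1.831. With 25% missing data, the main effect alone changed it slightly, for example from −5.31 (SE 2.119) to −5.342 (SE 2.069).

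**The case against.** The strongest objection is that the planned test works within patients. A stable patient factor that shifts all scores equally cancels from the interaction, so leaving it out costs nothing. This stands, and it limits the size of the harm. A reader who simulates a comparison of post scores might infer type I errors near 3.4% and 2.2% (strata explaining 16% and 25% of variance). Those figures do not describe the planned test unless the factor leaves baseline severity untouched, and the documents do not say that it does. Nor do they say that the shift is equal: they say only that the factors affect treatment outcome.

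A reader might also infer a raised false-positive rate. Reporting the better of an adjusted and an unadjusted post-score result would give 6.4–8.3% at 29 per arm (assumed correlations 0.3–0.7). The article proposes no such choice. Likewise, imbalance can be judged from baseline data alone, so the text does not show that covariates would be chosen with outcomes in view. It merely does not rule this out.

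Power is also not at the margin. With 50 per arm and the plan's own effect (7.9/10.6 = 0.745 SD), the unadjusted post-score comparison has about 96%.

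Finally, an article may leave the covariate list and threshold to a fuller document. That excuses the missing detail but not the rule, which the article states and which a later plan would have to replace.

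**Conclusion.** The point holds as a should-fix. The rule is stated outright, covers the primary analysis, tends to exclude the factors regarded as prognostic, and leaves the primary model undefined until the arms are compared. Applied mechanically, it makes the group × time test anything from correctly calibrated to conservative. Under the assumptions shown, the cost of omitting the strata is 0 to about 4 points of power at R = 0.16 and 0 to about 6.5 at R = 0.25. Where a trial falls in that range depends on how far the factors predict change rather than level, on which the documents give no figures. The calculation uses two time points, complete data and one exactly balanced stratum.

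The disagreement over chronicity needs no simulation. Until it is resolved, the set of strata to adjust for cannot be stated.

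**What to change.** First reconcile Study design and Randomization on whether chronicity was a stratification factor, according to how the random-number table was actually built.

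Then replace the covariate sentence with wording such as: *The primary model includes the factors used to stratify randomisation and baseline PDS, whatever the observed imbalance. No covariate is added to the primary analysis because of imbalance.*

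State the form of entry, because main effects alone leave the group × time estimate unchanged with complete data. Either of these acts on the primary contrast:

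- a baseline-constrained mixed model with stratum × time terms; or
- a post-treatment contrast adjusted for baseline PDS and the strata.

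The cost is wording and a few degrees of freedom, with no change to recruitment or data collection. The change should be dated before outcomes are compared by arm.

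### Baseline covariates entered as main effects cancel from the group × time interaction, so the promised adjustment for imbalance leaves the primary estimate unadjusted

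*Protocol article*

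**What the plan says.** The Data analysis plan of the protocol article fixes the parts of the primary model that matter here:

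- Model: "The primary outcome is a continuous longitudinal measure (PDS), therefore linear mixed-model analysis (LMM) will be run".
- Random part and covariates: a random intercept for each patient, and "covariates will be included in all analyses based on imbalance between trial arms".
- Effect: "The effects of the treatments will be examined using the interaction effect of group × time from the mixed-effects analysis", with post-treatment PDS as the primary outcome.
- Missing values: "Missing data will be estimated by SPSS multiple imputation on the primary measure".

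It names no covariate × time term. It does not say whether baseline PDS is a response row or a covariate, or which visits enter the primary model. On visits, Study design describes a "two-arm randomized controlled superiority trial with a pre-post and 12-month follow up", and Treatments adds assessments to "monitor their progress at the mid-point of therapy, end of treatment and 12 month follow-up". The Randomization section says that "both gender and BPD characteristics have been found/are assumed to impact treatment outcome".

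**The concern.** A group × time interaction with patient intercepts compares the arms on change within patients. For that comparison to be a treatment effect, pre-treatment PDS has to be one of the modelled visits. Gender, borderline traits and any other baseline covariate have one value per patient. As a main effect, such a covariate raises or lowers all of a patient's visits by the same amount and so says nothing about change. The covariate clause and the choice of effect term therefore do not work together, and this is so whether the covariates are chosen by imbalance or named in advance.

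At stake is the meaning of the primary result. If the arms differ by chance on something that governs response, including baseline PDS itself, the report would describe an MCT-EMDR difference as adjusted although it is numerically the unadjusted one. The precision that baseline adjustment offers would also be lost.

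**Working it through.** **Inputs from the protocol.** Sample size estimation: means 10.4 and 18.3 (difference 7.9), SD 10.6, two-sided 5%, 80% power, 29 per arm. Abstract: 100 patients, taken as 50 per arm.

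**Assumptions.** The article gives no pre-post correlation ρ and no baseline SD. I use ρ = 0.3, 0.5 and 0.7, and a baseline SD equal to the post-treatment SD.

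**The plan's own figure.** 2 × (1.960 + 0.842)² × (10.6/7.9)² = 28.3, rounded up to 29 per arm and 58 in total. It reproduces. It is used below only for scale.

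**Step 1: algebra.** Let X be a baseline covariate, G the arm and u the patient intercept:

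Y(i,t) = α + β(t) + γG(i) + δ(t)G(i) + cX(i) + u(i) + e(i,t)

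The change from baseline to post-treatment is

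Y(i,1) − Y(i,0) = [β(1) − β(0)] + [δ(1) − δ(0)]G(i) + e(i,1) − e(i,0).

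Both cX(i) and u(i) are gone. With every visit present, the estimated interaction is the raw difference in mean change, with or without X. Only a term c(t)X(i), that is covariate × time, survives the subtraction.

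**Step 2: model fits.** REML random-intercept models were fitted to simulated data with 50 per arm and SD 10.6.

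| Visits, ρ | No covariate (SE) | X as main effect (SE) | X and X × time (SE) |
|---|---|---|---|
| 2, 0.5 | 0.578 (2.228) | 0.578 (2.228) | −0.801 (2.348) |
| 3, 0.5 | 1.463 (2.248) | 1.463 (2.248) | 0.810 (2.236) |
| 4, 0.5 | −1.963 (2.100) | −1.963 (2.100) | −2.065 (2.118) |

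In all nine settings (2, 3 or 4 visits; three correlations), estimate and SE agreed to four decimals with and without X. With 25% of post-baseline values missing and no imputation, adding X moved the estimate by only 0.01 to 0.07 points.

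**Step 3: what stays in the estimate.** If the arms differ by 3 points on baseline PDS, the change contrast differs from a baseline-adjusted one by (1 − ρ) × 3, which is 2.1, 1.5 or 0.9 points. The planned difference is 7.9.

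**Step 4: precision.** For two visits and n = 50 per arm:

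- Change contrast: SE = 10.6 × √[2(1 − ρ)] × √(2/50) = 2.51, 2.12, 1.64.
- Baseline-adjusted: SE = 10.6 × √(1 − ρ²) × √(2/50) = 2.02, 1.84, 1.51.

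The ratio is √[(1 + ρ)/2] = 0.81, 0.87, 0.92. Simulation, which includes the cost of estimating the slope, gives about 0.81, 0.87, 0.93.

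**Step 5: error rates with no true effect (two visits).**

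| Share of trials rejected | ρ = 0.3 | ρ = 0.5 | ρ = 0.7 |
|---|---|---|---|
| All trials, change contrast | 5% | 5% | 5% |
| Baseline PDS significantly imbalanced, change contrast | 23% | 17% | 13% |
| Same trials, baseline-adjusted post-treatment contrast | 5% | 5% | 5% |

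**Step 6: baseline PDS as response row and covariate at once.** The estimate does not move in any setting. With two visits the intercept variance is estimated at zero, the SE falls to 0.91, 0.94 or 0.96 of its value, and overall type I error is about 6% to 8%. With three or four visits the SE ratio is 0.995 to 1.000 at ρ of 0.3 or more.

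**The case against.** The strongest reply is that the article does not say main effects only. It does not exclude covariate × time terms, and with them the adjustment works. Covariates used in the imputation model could also move the estimate, and a condensed article need not give model syntax. This stands as a limit: the point rests on the ordinary reading of including covariates and does not show that no adjusted result could be produced. It does not remove the point, because the article itself states the random structure, the covariate rule and the effect term, and that combination read plainly does not adjust.

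Three stronger readings are tempting and are not supported:

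- A reader might infer that entering baseline PDS always makes the standard error too small. That happens only in a pre-post model. The article calls the PDS longitudinal and describes mid-point and 12-month assessments, and with three or four visits the SE is practically unchanged. Even with two visits, a baseline SD of 8 instead of 10.6 brings the SE ratio to 0.95, 0.98 and 0.998.
- A reader might blame the covariate rule for the high rejection rates in imbalanced trials. Most of that excess is there with no covariate at all and comes from regression to the mean in the change contrast. In two-visit models the double use of baseline PDS adds only a few percentage points, up to about eight at ρ = 0.3.
- A reader might infer that the planned comparison is biased. It is not: over all randomizations the change contrast keeps its 5% error rate, and significant baseline imbalance arises in only about 5% of trials. Gender and borderline traits are also stratified, so a large imbalance in those two factors is a poor illustration.

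Imputation is planned for the primary measure only. On the secondary scales the cancellation is therefore near rather than exact.

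**Conclusion.** The point holds in limited form. With covariates as main effects, the group × time estimate is the same with and without them, exactly in complete or imputed PDS data, so the stated adjustment does nothing to the primary result. The algebra needs no numerical assumption, only the main-effect reading.

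The consequences depend on the assumed correlations of 0.3 to 0.7, equal SDs and 50 per arm. The unadjusted contrast is valid on average but gives up 7% to 19% in standard error. In trials with a significant baseline PDS imbalance it rejects a true null about 13% to 23% of the time, where baseline adjustment holds about 5%. The further shrinkage of the SE from using baseline PDS twice belongs to a two-visit model only. This should be corrected before analysis.

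**What to change.** Choose one form and state it:

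- **Preferred.** Model post-baseline PDS as the response, with baseline PDS and the named covariates on the right-hand side, and take the MCT-EMDR difference at post-treatment as the estimate. This also deals with imbalance in baseline PDS.
- **Alternative.** Keep the baseline row and enter every covariate with its covariate × time term, without also using baseline PDS as a covariate. This adjusts for the named covariates but leaves the contrast as a change from baseline where PDS itself is imbalanced.

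Name the covariates, for example the stratification factors. Study design and Randomization list these differently (only the former includes chronicity), so the list should be explicit. State which visits enter the model and that baseline PDS is never both response and covariate. Use the same form for the secondary scales.

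The cost is one or two sentences, matching model syntax and a few degrees of freedom, with no new data or patients.

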**Methods/design:**

This study is a two-arm, parallel, randomized, superiority trial comparing the effectiveness of MCT with EMDR. One hundred patients with a primary diagnosis of chronic PTSD will be included and will receive 12 sessions of one of the treatments. The primary outcome is severity of PTSD symptoms assessed with the Posttraumatic Diagnostic Scale (PDS) measured post-treatment (3 months). Secondary outcomes include symptom severity (PDS) and measures of anxiety, depression, metacognitive beliefs at 3-month and 12-month follow up.

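### The primary test is a group × time interaction with visits, time coding and coefficient left open, so it need not be the post-treatment PDS comparison the trial is designed to make.

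*Protocol article*

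**What the plan says.** The target is one time point. The Study design section states: "The primary hypothesis is that MCT will be superior to EMDR in reducing PTSD symptoms measured with the PDS post-treatment". The Abstract dates post-treatment at 3 months and lists later PDS measurements as secondary. The Sample size estimation section compares two post-treatment means, 10.4 and 18.3 with SD 10.6, and concludes that "58 patients are required in total (29 per arm) to have an 80% chance of detecting a significant difference".

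The Data analysis plan section takes a longitudinal route: "The primary outcome is a continuous longitudinal measure (PDS), therefore linear mixed-model analysis (LMM) will be run". Its model is described in one sentence: "Random effects will be applied to the patient-specific intercepts and covariates will be included in all analyses based on imbalance between trial arms". The treatment effect is then examined "using the interaction effect of group × time from the mixed-effects analysis with PDS post-treatment as the primary outcome". No visit list, time coding, primary coefficient or residual covariance structure is given. Adjustment depends on observed imbalance, so baseline PDS has no fixed place in the model.

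Several visits could enter. The Treatments section has assessments "at the mid-point of therapy, end of treatment and 12 month follow-up", the Abstract names 3-month and 12-month follow-up, and the retention section names 6 and 12 months. The Discussion says that patients may seek further treatment during follow-up and that this could bias the 12-month data.

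**The concern.** Over more than two visits there is no single group × time interaction. With categorical time, the overall test has several degrees of freedom and responds to a divergence of the arms at any visit. With linear time it is a difference in slopes. With categorical time and one coefficient read out, or with pre and post visits only, it is the difference in change from baseline to post-treatment. The text permits all three, and they can give opposite answers.

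The primary claim could therefore turn on 12-month data, which the protocol treats as secondary and itself flags as open to bias. Even the most favourable reading is a change-score comparison, whereas the sample size was computed for a comparison of means.

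**Working it through.** **1. The plan's own figure.** Inputs from the Sample size estimation section: difference 18.3 − 10.4 = 7.9, SD 10.6, two-sided 5%, 80% power.

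n per arm = 2 × 10.6² × (1.960 + 0.842)² / 7.9² = 28.3, rounded up to 29, or 58 in total. The figure reproduces. Power at 29 per arm by t test is 79.7%. It belongs to a single comparison of post-treatment means.

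**2. If follow-up visits enter.** Assumptions not in the documents: PDS at months 0, 3 and 15 (12 months after post-treatment), SDs 8, 10.6 and 10.6, pre–post correlation 0.4. Share of 4,000 simulated trials per scenario that reject, at 29 and 50 per arm:

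| Truth | Joint interaction | Linear slope | Single pre-to-post contrast |
|---|---|---|---|
| Equal at post-treatment, 7.9 apart at 12 months | 92% / 99.8% | 94% / 99.6% | about 6.5% |
| 7.9 apart at post-treatment, equal at 12 months | – | 16% / 27% | – |

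The slope can also be checked by hand. The mean visit time is 6 months, so the centred times are −6, −3 and 9, with sum of squares 126. If a 7.9 difference is present at post-treatment and held to 12 months, the fitted slope difference is (−3 × 7.9 + 9 × 7.9)/126 = 0.376 per month. At month 3 that is 1.13 points, not 7.9.

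**3. If the test is the pre-to-post change.** SD of change = √(s₀² + 10.6² − 2ρ·s₀·10.6), where s₀ is the baseline SD. Baseline-adjusted SD = 10.6·√(1 − ρ²). In both cases SE = SD × √(2/n). For s₀ = 10.6 and ρ = 0.3, the SDs are 12.54 and 10.11, and at n = 29 the SEs are 3.29 and 2.66. Power to detect 7.9 at 29 per arm, with ρ and s₀ assumed:

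| ρ | Change, s₀ = 10.6 | Change, s₀ = 8 | Baseline-adjusted |
|---|---|---|---|
| 0.3 | 65% | 75% | 83% |
| 0.4 | 72% | 81% | 86% |
| 0.5 | 80% | 87% | 90% |

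The Abstract plans 100 patients. Applying the 20–25% attrition quoted in the Discussion leaves 75 to 80, or 37.5 to 40 per arm. In the least favourable row (ρ = 0.3), change then has 77–79% power with s₀ = 10.6 and 85–88% with s₀ = 8. At 40 per arm the baseline-adjusted SE is 10.11 × √(2/40) = 2.26, giving 93% power.

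**4. Standard error under random intercepts alone.** With complete balanced data the model takes the variance of any two-visit change as 2 × (mean variance − mean covariance). The true pre-to-post variance is V₀ + V₁ − 2·Cov₀₁.

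- *Too small.* Assume SDs 8, 10.6, 10.6 and correlations pre–post 0.3, pre–12 months 0.25, post–12 months 0.75. Mean variance = (64 + 112.36 + 112.36)/3 = 96.24. Mean covariance = (25.44 + 21.20 + 84.27)/3 = 43.64. Model: 2 × 52.60 = 105.2. True: 64 + 112.36 − 50.88 = 125.5. SE ratio = √(105.2/125.5) = 0.92, type I error 7.3%. As pre–post correlation rises from 0.3 to 0.6, the ratio runs from 0.92 to 0.98 (type I error 7.3% to 5.5%). With four visits it runs from 0.85 to 0.95 (9.5% to 6.4%).
- *Too large.* Assume equal SDs, pre–post correlation 0.6 and the other two 0.5 and 0.4, average 0.5. Model: 2 × 112.36 × 0.5 = 112.4. True: 2 × 112.36 × 0.4 = 89.9. SE ratio 1.12, type I error about 3%.
- *Exact.* With pre and post only, there is one pair of visits and the ratio is 1.00.

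**The case against.** The sentence that names the interaction also names post-treatment PDS as the primary outcome, and the Abstract and Study design section place follow-up among the secondary questions. A sensible analyst could use two visits, or read out the post-treatment coefficient, and obtain a 1-df test at the right time. This stands. The text allows the right coefficient, so one cannot say that the plan definitely tests something else. But it names the outcome and not the coefficient, and the joint and slope readings remain equally open.

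The visits in the model are also inferred. The Data analysis plan section lists none, the Treatments section does not name PDS, and the schedule figure is not shown. Error rates that need four or five PDS visits therefore cannot be attributed to this trial.

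A reader might infer that the standard error is probably too small and the type I error inflated. The documents do not support that: they give no between-visit variances or correlations, the error can go either way, and it vanishes with two visits. A residual covariance structure could also be added to the random intercept.

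A reader might also infer that the trial is underpowered. That is not shown either. With a baseline SD of 8 and correlation 0.4, a change score has 81% power at 29 per arm, and 100 patients are planned.

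Finally, covariance structure is often left to a statistical analysis plan. Its absence alone would be no finding. Here it matters because the primary test is stated, and in a form that does not pin down the stated question.

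**Conclusion.** The point holds as one about the definition of the primary test. The protocol asks about PDS at post-treatment but fixes an interaction that equals that question only under some readings.

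- If follow-up visits enter and the joint or slope test is used, 12-month data can decide the result: 92% or more rejections with no post-treatment difference, under the three-visit assumptions.
- If the pre-to-post coefficient is used, the test is at the right time but gives up efficiency: 65–80% against 83–90% power at 29 per arm with equal SDs and correlation 0.3–0.5. The change-score figures become 75–87% with a baseline SD of 8, and the gap narrows further at the planned 100 patients.
- With more than two visits, the random-intercept standard error is too small if the pre-to-post change varies more than the average two-visit change, and too large if it varies less. With equal SDs this means a baseline-to-post correlation below or above the between-visit average. The direction for this trial is unknown.

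All correlations, the baseline SD and the visit times are assumptions. The sample size of 58 reproduces and needs no change.

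**What to change.** Replace the sentence on the interaction with a statement to this effect: PDS is analysed in a linear mixed model that lists its visits; time is categorical; within-patient covariance is unstructured; baseline PDS is adjusted for, either as a covariate or by constraining the baseline means to be equal across arms, whether or not the arms look imbalanced. The single primary test is the 1-df MCT–EMDR contrast at the post-treatment visit. The 12-month contrast from the same model is secondary.

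This uses data already planned and changes only wording. The Trial status section says that recruitment was ongoing, so the change could be made before the analysis. The cost is a few more covariance parameters: with v visits, v(v + 1)/2 instead of two, so 6 for three visits and 10 for four.
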